There are several HIV prevention behaviors that are critical for decreasing HIV transmission risk that can be addressed with HIV-positive patients in care and treatment settings. In generalized, high prevalence epidemics, many new infections result from multiple, often concurrent sexual partnerships. Thus, reducing the number of sex partners is an important HIV prevention strategy (Halperin & Epstein, 2004; Morris & Kretzschmar, 1997). In addition, using a condom at each sexual encounter is a highly effective method of lowering HIV transmission risk. However, rates of condom use are very low in sub-Saharan Africa, with estimates ranging from 4% to 28% for the most recent sex act (Cleland & Ali, 2006; Desgrees-du-Lou et al., 2002; Kapiga & Lugalla, 2003). This is particularly important in sub-Saharan Africa, as the rate of serodiscordance among spouses and cohabitating partners is high. For example, in Zambia and South Africa, approximately 20% of couples in the general population were found to be HIV serodiscordant (Lurie et al., 2003; McKenna et al., 1997). In Kenya, approximately 50% of HIV-positive persons have an HIV-negative spouse or cohabitating partner (Central Bureau of Statistics, 2003). This high rate of serostatus discordance suggests that large numbers of married and cohabitating couples in the general population are at high risk for HIV transmission. In addition, rates of disclosure of HIV status are often low, resulting in many individuals who do not know that their spouse or partner is living with HIV. For example, several studies have shown that only one-fourth to one-half of HIV-positive individuals disclose their serostatus to their regular sex partners (Antelman et al., 2001; Medley et al., 2004; WHO, 2003). There are many reasons why people do not disclose their status to partners. For instance, many women, in particular, fear losing their homes or livelihood if they disclose their HIV status to their spouse or partner (WHO, 2003).

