**Participant inclusion criteria**

Clinic patients

- At least 18 years old
- HIV-positive patients receiving care at a project clinic and seen at the clinic at least twice prior to enrollment (half of patients will be taking ARVs)
- Sexually active within the past three months
- Planning to attend the clinic for at least 1 year
- Able to provide informed consent to participate in the project
- Able to conduct interview in one of the following languages:

Kenya: English, Kiswahili and Kikuyu

Namibia: English, Oshiwambo, Damara-nama, Otjihero, Afrikaans

Tanzania: English, Kiswahili

Health care providers and lay counselors

- At least 18 years old
- Fluent/literate in the language selected for the project training
- Planning to remain at the clinic for one year
- Willing to complete project questions and agree to be observed during patient visits
- Physicians, clinical officers, and nurses who are employees of the project clinic and providing care and treatment to patients in the HIV project clinics
- Lay counselors who are providing HIV prevention services in the project clinics

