**Sampling, including sample size and statistical power**

Participants will be sampled from the database of patients already receiving care at the project clinics. Information about gender, whether on ART, and last clinic visit will be used to create a list of potential participants. From that list, patients will be randomly selected to create a list of patients to approach about participating in the project. When patients arrive at the clinic the list will be checked and if their name is on it they will be asked if they are interested in participating in the project (see enrollment section below for further description). If they are not, their name will be removed from the list. Each clinic will enroll approximately half of each gender and half who are on ART. A tally of persons in each of the gender by ART cells will be kept updated daily. As each of the cells near the enrollment targets the study coordinator will monitor the potential participant list to ensure that appropriate numbers of participants are in each group.

The primary outcome variable for the project will be participant self-report of any unprotected sex in the past 3 months. Prior studies have found rates of condom use to be very low in the areas in which this project will be conducted (Arthur et al., 2007; Feldblum et al., 2000; Kapiga et al., 2006; Mwaluko et al., 2003; Norman, 2003; Stanton et al., 1999; Ross et al., 2007; Watson-Jones et al., 2007). We will assume a rate of at least 50% for any unprotected sex in the past 3 months in the comparison condition for sample size estimation.

Although the proposed project includes measurements at three time points (baseline, 6 months and 12 months), sample size estimates are presented for the simple difference between proportions in the two project conditions at the 12-month follow-up only. This approach is conservative because analytic approaches taking into account the multiple observations on each participant will be more powerful. We use the cross-sectional approach for sample size estimation because no prior data are available on which to base prediction of the pattern of intervention effects over time and the magnitude of the over-time correlation of groups and group members that we can expect in this project. Our sample size estimates do take into account expectations of attrition in the project cohort, which we expect to be moderate (at most 30% at the 12-month follow-up).

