**PROCEDURES/METHODS: VARIABLES/INTERVENTIONS**

**Variables**

Variables will be collected from patients and from clinic charts. The variables will include both behavioral and biologic dependent variables. In addition, we will examine several potential variables that may mediate the hypothesized changes in outcome variables. The following paragraphs describe our primary outcome variables, our primary independent variables, and potential mediating variables.

Primary Outcome Variables

The primary outcome variables will be compared for those in the intervention and those in the comparison arms. These variables have been discussed previously and include self-reported sexual risk behaviors (e.g., any unprotected sex in the past 3 months, number of sex partners, proportion of sex acts that are unprotected with HIV-negative or unknown status partners), disclosure of HIV status to sex partners, partner testing for HIV, alcohol use, HIV medication adherence, STIs (i.e., urethral discharge) unintended pregnancies, family planning and safer pregnancy counseling, and family planning services (e.g., contraception).

Independent Variables

As discussed, we propose conducting a longitudinal cohort project with a two arm design. The intervention group will consist of participants from clinics in which the staff have been trained to provide the HIV prevention intervention package and the comparison group will be participants from clinics providing the current standard of care. For our primary outcomes, we will use an intent-to-treat (ITT) analysis approach. That is, participant data will be analyzed based on the project arm to which they were assigned. Thus, intervention or comparison arm will serve as our primary independent variable in these analyses.

The ITT approach preserves the unbiased comparability between the intervention arm and the comparison arm that results from random assignment, thereby strengthening our project’s internal validity. Furthermore, our primary research questions focus on hypothesized outcomes associated with providing a package of HIV prevention interventions for HIV-positive persons, and analyzing the data based on the project condition to which participants were randomized will allow us to examine the impact of this intervention.

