***Health Care Provider-delivered Prevention Messages***

*1) 5 HIV Prevention Steps for PLWHA in HIV Care and Treatment Settings*

and

*HIV Prevention Messages for PLWHA in HIV Care and Treatment Settings*

Background: Delivering prevention messages to HIV-positive individuals in care and treatment settings can significantly impact the HIV transmission risk behavior of infected persons. Two US-based health care provider-delivered interventions involving providers discussing prevention topics (e.g., serostatus disclosure, consistent condom use) were found to be effective at decreasing the rate of unprotected sex in HIV-positive individuals (Fisher et al., 2006; Richardson et al., 2004). In addition, these studies showed that integrating brief prevention discussions into routine clinic visits in busy medical settings was feasible. Training health care providers to routinely deliver prevention messages to HIV-positive patients in care and treatment settings in sub-Saharan African countries may also be an effective prevention strategy to facilitate reduction of sexual risk behaviors. The intervention and materials developed for this project were adapted from Partnership for Health (Richardson et al., 2004). The investigators obtained input from health care providers in Kenya, Uganda, and Botswana for the adaptation of the materials for the African context and field tested the interventions in 3 clinics in Kenya. The original intervention was expanded to include additional prevention messages and services to more comprehensively address prevention for HIV positive persons and to meet the demands of the African setting.

Intervention Components:

HIV health care providers (e.g., doctors, clinical officers, nurses) and professional staff (e.g., social workers, pharmacists) who are involved with the care of HIV infected patients in the HIV clinic will assess prevention issues and deliver specific prevention messages during routine clinic visits. Specifically, providers will do the following:

- Assess whether patient is sexually active
- Assess whether sex partner(s) have been tested for HIV and refer partner(s) for testing
- Assess whether patient has disclosed to sex partner(s) and encourage disclosure
- Encourage adoption of safer sex behaviors (e.g., abstain or be faithful to one partner, reduce number of partners, and use condoms with every sexual encounter)
- Explain the negative consequences of having sex without a condom

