**Patient Sex Behavior**

| ***Interviewer reads:*  “**Now I would like to ask you some questions about your recent sexual activity. We know these questions are sensitive and want to remind you that your answers are completely private and will not be shared with anyone. No one will know what particular answers you give. It is perfectly normal for persons with HIV to have sex. We are not judging you on your sexual behaviors. We want you to be as honest as you can answering these questions. If we should come to any questions that you don’t want to answer, just let me know and we will go to the next one.  Different people have different definitions of ‘sex’ or ‘sexual intercourse.’ For this study, sex can include several things, such as:   - Vaginal sex, which is when a man puts his penis in a woman’s vagina. - Anal sex, which is when a man puts his penis in another person’s rectum or butt.” |
| --- |

J1. How old were you when you had sexual intercourse for the very first time?

__________Age in years

*_____-1. Don’t know*

*_____-2. Refused*

J2. In total, how many different people have you had sexual intercourse with in your entire life?

__________Total number of lifetime partners

*_____-1. Don’t know*

*_____-2. Refused*

J3. Have you had sexual intercourse in the last 3 months?

_____ 0. No  *Skip to K1 in next section.*

_____ 1. Yes

*_____-1. Don’t know*

*_____-2. Refused*

J4. In total, how many people have you had sex with in the last 3 months?

__________ Total number of partners

*_____-1. Don’t know*

*_____-2. Refused*

J5. In total, how many people have you had sex with in the last 2 weeks?

__________ Total number of partners

*_____-1. Don’t know*

*_____-2. Refused*

| ***Interviewer reads:*** “I am going to ask you about the people you had sex with over the past 90 days. Please tell me about them starting with your most recent sexual partner.” |
| --- |

*[****Interviewer:*** *Read down each column of the table (for each partner, one at a time),* ***not*** *across each row.]*

|  | **Partner 1** | **Partner 2** | **Partner 3** | **Partner 4** | **Partner 5** |
| --- | --- | --- | --- | --- | --- |
| J6. What is the first name or a nickname of this partner? | ___ *-1. Don’t know*  ___ *-2. Refused* | ___ *-1. Don’t know*  ___ *-2. Refused* | ___ *-1. Don’t know*  ___ *-2. Refused* | ___ *-1. Don’t know*  ___ *-2. Refused* | ___ *-1. Don’t know*  ___ *-2. Refused* |

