| J23.Do you provide any financial support to this partner? | ___ 0. No  ___ 1. Yes  ___ *-1. Don’t know*  ___ *-2. Refused* | ___ 0. No  ___ 1. Yes  ___ *-1. Don’t know*  ___ *-2. Refused* | ___ 0. No  ___ 1. Yes  ___ *-1. Don’t know*  ___ *-2. Refused* | ___ 0. No  ___ 1. Yes  ___ *-1. Don’t know*  ___ *-2. Refused* | ___ 0. No  ___ 1. Yes  ___ *-1. Don’t know*  ___ *-2. Refused* |
| J24. In the past 90 days, how many times did you have vaginal sex with this partner? | ________ [# of times]  **If 0, skip to J29**  ___ *-1. Don’t know*  ___ *-2. Refused* | ________ [# of times]  **If 0, skip to J29**  ___ *-1. Don’t know*  ___ *-2. Refused* | ________ [# of times]  **If 0, skip to J29**  ___ *-1. Don’t know*  ___ *-2. Refused* | ________ [# of times]  **If 0, skip to J29**  ___ *-1. Don’t know*  ___ *-2. Refused* | ________ [# of times]  **If 0, skip to J29**  ___ *-1. Don’t know*  ___ *-2. Refused* |
| J25. How many of these times in the past 90 days did you use a condom during vaginal sex? | ________ [# of times]  ___ *-1. Don’t know*  ___ *-2. Refused* | ________ [# of times]  ___ *-1. Don’t know*  ___ *-2. Refused* | ________ [# of times]  ___ *-1. Don’t know*  ___ *-2. Refused* | ________ [# of times]  ___ *-1. Don’t know*  ___ *-2. Refused* | ________ [# of times]  ___ *-1. Don’t know*  ___ *-2. Refused* |
| J26. Did you or your partner use a condom the last time you had vaginal sex together? | ___ 0. No  ___ 1. Yes  ___ *-1. Don’t know*  ___ *-2. Refused* | ___ 0. No  ___ 1. Yes  ___ *-1. Don’t know*  ___ *-2. Refused* | ___ 0. No  ___ 1. Yes  ___ *-1. Don’t know*  ___ *-2. Refused* | ___ 0. No  ___ 1. Yes  ___ *-1. Don’t know*  ___ *-2. Refused* | ___ 0. No  ___ 1. Yes  ___ *-1. Don’t know*  ___ *-2. Refused* |
| J27. During the past 14 days, how many times did you have vaginal sex with this partner? | ________ [# of times]  **If 0, skip to J29**  ___ *-1. Don’t know*  ___ *-2. Refused* | ________ [# of times]  **If 0, skip to J29**  ___ *-1. Don’t know*  ___ *-2. Refused* | ________ [# of times]  **If 0, skip to J29**  ___ *-1. Don’t know*  ___ *-2. Refused* | ________ [# of times]  **If 0, skip to J29**  ___ *-1. Don’t know*  ___ *-2. Refused* | ________ [# of times]  **If 0, skip to J29**  ___ *-1. Don’t know*  ___ *-2. Refused* |

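### A listed outcome, the proportion of acts unprotected with HIV-negative or unknown-status partners, is undefined for anyone with no sex at follow-up, and the intervention affects who that is

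*Protocol*

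**What the plan says.** The Variables section of the protocol, under Primary Outcome Variables, names several sexual risk measures as examples. One is "proportion of sex acts that are unprotected with HIV-negative or unknown status partners". The variables in that list are to be compared between arms by intent-to-treat. The protocol states no numerator or denominator for the ratio and no value for a participant with no acts.

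The section on sampling and power names a different variable for the sample size: "The primary outcome variable for the project will be participant self-report of any unprotected sex in the past 3 months".

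Three other parts of the protocol bear on the ratio:

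- **Entry criteria.** Patients must be "Sexually active within the past three months". This applies at enrolment only.
- **Patient Questionnaire (Appendix H).** Item J3 asks "Have you had sexual intercourse in the last 3 months". A No skips to section K, past every partner and act item. The act counts come from J24 and J25 (vaginal) and J29 and J30 (anal), asked for each partner, for example "In the past 90 days, how many times did you have vaginal sex with this partner".
- **Intervention components.** Providers encourage patients to "abstain or be faithful to one partner, reduce number of partners, and use condoms with every sexual encounter". They also "Assess whether sex partner(s) have been tested for HIV and refer partner(s) for testing".

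**The concern.** A proportion needs a denominator above zero. Because sexual activity is an entry requirement, cases with no acts at all should arise almost only after baseline, and having no acts is one of the results the package seeks. Whether a participant has a value on this outcome therefore depends on behaviour after randomization that the intervention is meant to change.

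Partner testing adds to this. If the denominator covers only acts with HIV-negative or unknown-status partners, a partner who moves from unknown to known HIV-positive leaves it.

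At stake is the comparability that the protocol gives as its reason for intent-to-treat. A comparison among those who still have acts sets two selected subsets side by side and cannot credit a benefit that comes through abstinence.

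**Working it through.** The protocol gives no rate, effect size or power for this outcome, so there is no stated figure to reproduce. The check evaluates the ratio on the questionnaire paths and then uses arithmetic on assumed shares.

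**1. Who has a value.** The wording allows two denominators: all sex acts (the literal grammar), or acts with HIV-negative or unknown-status partners.

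| Participant at follow-up | Denominator: all acts | Denominator: acts with negative/unknown partners |
|---|---|---|
| No sex (J3 = No) | 0/0, undefined | 0/0, undefined |
| 10 acts, all with HIV-positive partners | 0/10 = 0 | 0/0, undefined |
| 10 acts with a negative partner, all with condoms | 0/10 = 0 | 0/10 = 0 |

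A participant who has stopped sex has no value under either reading. One with only HIV-positive partners lacks a value only under the second.

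**2. How many.** Let a be the abstinent share and s the share of participants with any HIV-negative or unknown-status partner. Both are assumptions: a = 10% to 25%, s = 50% to 75%. The nearest figure in the protocol is from the background section, for Kenya: "approximately 50% of HIV-positive persons have an HIV-negative spouse or cohabitating partner". It does not count unknown-status partners.

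- All acts: undefined share = a = 10% to 25%. Of the 1260 retained per condition (2520/2), that is 126 to 315.
- Narrower denominator: undefined share = 1 − s(1 − a). With s = 0.75 and a = 0.10 it is 1 − 0.675 = 32.5%. With s = 0.50 and a = 0.25 it is 1 − 0.375 = 62.5%.

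**3. What exclusion does to the comparison.** Assume half the participants have 60% of acts unprotected (risky) and half have 10% (careful). The comparison mean is 0.5 × 0.60 + 0.5 × 0.10 = 35.0%. In the intervention arm, let 10% of participants stop sex and nothing else change.

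| Who stops | Stoppers excluded | Stoppers scored 0 |
|---|---|---|
| 20% of the careful half | (0.30 + 0.04)/0.90 = 37.8% | 0.30 + 0.04 = 34.0% |
| 20% of the risky half | (0.24 + 0.05)/0.90 = 32.2% | 0.24 + 0.05 = 29.0% |
| 10% regardless of risk | (0.90 × 0.35)/0.90 = 35.0% | 0.90 × 0.35 = 31.5% |

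The first row shows apparent harm under exclusion and benefit under zero-scoring. The third shows no difference under exclusion, although 10% of the arm have no acts left to be unprotected.

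**4. When the sign reverses.** Let M be the comparison mean and m the mean proportion the stoppers would otherwise have had. With no other effect, the mean after exclusion is (M − a·m)/(1 − a). This exceeds M exactly when m is below M, that is, when the stoppers are on average lower-risk.

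**The case against.** The strongest reply is that scoring a zero denominator is a derivation rule, which belongs in the statistical analysis plan. A No at J3 is recorded data that establishes zero acts, and nothing in the protocol stops the analyst from scoring 0. Part of this stands. A reader might infer that the plan drops abstainers, but the protocol states neither exclusion nor a zero score. What remains is that the protocol itself chose a ratio whose denominator the intervention affects, and placed it among the outcomes compared by intent-to-treat. If 0/0 were coded as missing and the multiple imputation planned for the primary outcome were extended to this variable, it would create a risk proportion for acts that never took place.

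Three further objections hold and limit the point:

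- **Size.** A reader might infer that a third to nearly two thirds of participants cannot be scored. That range needs the narrower denominator and assumed shares. Under the literal reading, only those with no sex are undefined.
- **Sign.** A reader might infer that the effect will reverse. Reversal needs the stoppers to be lower-risk on average, and the documents give no evidence either way.
- **Reach.** The proportion is one example in a list. It is absent from the Objectives and not named in the Hypotheses. The powered outcome and the number of partners can both be scored 0 for someone who has stopped sex, so they can register abstinence.

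**Conclusion.** The point holds for this listed outcome. The ratio is undefined for anyone with no sex in the past 3 months at follow-up. Under the narrower denominator it is also undefined for those with only HIV-positive partners, and for them the baseline covariate in the planned mixed model can be undefined too. Because the package targets abstinence and partner testing, a comparison among those with acts is not the intent-to-treat comparison that the protocol promises.

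The undefined share is unknown: it is the abstinent share alone if the denominator is all acts, and larger if it is the narrower one. The illustrated distortion (37.8% against 34.0% for the same intervention arm, comparison 35.0%) rests wholly on assumed shares and on careful participants being the ones who stop. The sample size and the main test of any unprotected sex are unaffected. The change should be made, but the main conclusion does not depend on it.

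**What to change.** In the Variables section, replace the proportion as a compared outcome with one defined for every interviewed participant. This would be any unprotected act in the past 3 months with an HIV-negative or unknown-status partner, or the number of such acts, scored 0 when there was no sex or no such partner. Keep the proportion as a descriptive summary among those with acts, with its numerator and denominator stated.

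The cost is a change of wording. The same questionnaire items supply the data, and the sample size stands. The downside is small: a yes/no version carries less detail than a proportion, and the count version avoids part of that loss. Keeping the ratio with a stated denominator and scoring no acts as 0 would be a lighter change and would also remove the undefined values, but intervention-driven shifts in the denominator would still move the score.

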**Hypotheses**

Project hypotheses focus on the effectiveness of the prevention intervention package on behavioral outcomes, biologic outcomes, and delivery of services in the HIV care and treatment settings. Intervention clinics will integrate the HIV prevention intervention package into routine care of HIV-positive patients; comparison clinics will provide standard of care to HIV-positive patients.

Compared to participants attending comparison HIV clinics, participants at intervention clinics will be more likely over a 12-month period to report or show a(n):

Behavioral

- Decrease in unprotected vaginal and anal sex
- Decrease in number of sex partners
- Increase in number of sex partner(s) getting an HIV test
- Increase in disclosure of HIV status to sex partner(s)
- Decrease in alcohol use
- Increase in adherence to HIV antiretroviral medications

Biologic

- Decrease in unintended pregnancy or partner pregnancy
- Decrease in STIs (i.e., urethral discharge)

Service Delivery

Compared to the comparison clinics, the intervention clinics will:

- Provide more family planning counseling (e.g., safer pregnancy) and services (e.g., contraception) to HIV-positive women and their partners

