In addition to our primary ITT analysis, we plan to examine other independent variables and their relationship to our outcome variables described above. These variables include number of clinic visits, amount of time spent with health care providers and lay counselors during clinic visits, and prevention activities discussed.

Potential Mediating Variables

Our potential mediating variables include domains such as physical and mental functioning, HIV transmission risk knowledge and perception of HIV transmission risk, social support, sexual self-efficacy, communication with partner, STI symptoms, CD4, and physical and sexual violence. Within each of these domains, our questionnaire will use sets of items to measure various subcategories of these domains. Scores on these items will be used as mediating variables to examine whether they impact our proposed primary outcome variables.

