**Emergency care**

There are no expected harmful consequences as a result of participating in this evaluation. However, should an HIV-positive patient express a need for emergent medical care, the project coordinator will attempt to locate immediate care through the health care facility where the patient is participating in the project.

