| J19. How long ago did you tell this partner that you are HIV-positive? | ____ Days ago  ____ Months ago  ____ Yearsago  ___ *-1. Don’t know*  ___ *-2. Refused* | ____ Days ago  ____ Months ago  ____ Years ago  ___ *-1. Don’t know*  ___ *-2. Refused* | ____ Days ago  ____ Months ago  ____ Years ago  ___ *-1. Don’t know*  ___ *-2. Refused* | ____ Days ago  ____ Months ago  ____ Yearsago  ___ *-1. Don’t know*  ___ *-2. Refused* | ____ Days ago  ____ Months ago  ____ Years ago  ___ *-1. Don’t know*  ___ *-2. Refused* |
| J20. When you told this partner you are HIV-positive did your partner hit, slap, kick, or do anything else to hurt you physically? | ___ 0. No  ___ 1. Yes  ___ *-1. Don’t know*  ___ *-2. Refused*  **Go to J22** | ___ 0. No  ___ 1. Yes  ___ *-1. Don’t know*  ___ *-2. Refused*  **Go to J22** | ___ 0. No  ___ 1. Yes  ___ *-1. Don’t know*  ___ *-2. Refused*  **Go to J22** | ___ 0. No  ___ 1. Yes  ___ *-1. Don’t know*  ___ *-2. Refused*  **Go to J22** | ___ 0. No  ___ 1. Yes  ___ *-1. Don’t know*  ___ *-2. Refused*  **Go to J22** |
| *If ‘no’ to J18:*  J21. How confident are you that you could tell this partner about your HIV status in the next month? | ___ 1. Very confident  ___ 2. Confident  ___ 3. Somewhat confident  ___ 4. Not at all confident  ___ *-1. Don’t know*  ___ *-2. Refused* | ___ 1. Very confident  ___ 2. Confident  ___ 3. Somewhat confident  ___ 4. Not at all confident  ___ *-1. Don’t know*  ___ *-2. Refused* | ___ 1. Very confident  ___ 2. Confident  ___ 3. Somewhat confident  ___ 4. Not at all confident  ___ *-1. Don’t know*  ___ *-2. Refused* | ___ 1. Very confident  ___ 2. Confident  ___ 3. Somewhat confident  ___ 4. Not at all confident  ___ *-1. Don’t know*  ___ *-2. Refused* | ___ 1. Very confident  ___ 2. Confident  ___ 3. Somewhat confident  ___ 4. Not at all confident  ___ *-1. Don’t know*  ___ *-2. Refused* |
| J22. Does this partner provide any financial support to you or any of your children? | ___ 0. No  ___ 1. Yes  ___ *-1. Don’t know*  ___ *-2. Refused* | ___ 0. No  ___ 1. Yes  ___ *-1. Don’t know*  ___ *-2. Refused* | ___ 0. No  ___ 1. Yes  ___ *-1. Don’t know*  ___ *-2. Refused* | ___ 0. No  ___ 1. Yes  ___ *-1. Don’t know*  ___ *-2. Refused* | ___ 0. No  ___ 1. Yes  ___ *-1. Don’t know*  ___ *-2. Refused* |

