**Violence**

L1. Have any of your current partners hit, slapped, kicked, or done anything else to hurt you physically?

_____ 0. No  *Skip to L2*

_____ 1. Yes

*_____ -1. Don’t know*   *Skip to L2*

*_____ -2. Refused*   *Skip to L2*

*_____ -3. Not Applicable*  *Skip to L2*

L1a. Did this happen in the last 6 months?

_____ 0. No

_____ 1. Yes

*_____ -1. Don’t know*

*_____ -2. Refused*

L2. Has anyone else ever hit, slapped, kicked, or done anything else to hurt you physically?

_____ 0. No *Skip to L3*

_____ 1. Yes

*_____ -1. Don’t know*  *Skip to L3*

*_____ -2. Refused*  *Skip to L3*

L2a. Did this happen in the last 6 months?

_____ 0. No

_____ 1. Yes

*_____ -1. Don’t know*

*_____ -2. Refused*

L3. Has anyone ever forced you to have sexual intercourse or perform any other sexual acts?

_____ 0. No  *Skip to M1 in next section*

_____ 1. Yes

*_____ -1. Don’t know*  *Skip to M1 in next section*

*_____ -2. Refused*  *Skip to M1 in next section*

L3a. Did this happen in the last 6 months?

_____ 0. No

_____ 1. Yes

*_____ -1. Don’t know*

*_____ -2. Refused*

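### Partner and sexual violence is given only a mediator role, so the protocol plans no between-arm comparison of a harm that its questionnaire already measures

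*Protocol*

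**What the plan says.** **Role of violence.** In the Protocol, Variables, Potential Mediating Variables, the list of mediator domains includes "communication with partner, STI symptoms, CD4, and physical and sexual violence". The stated use follows: "Scores on these items will be used as mediating variables to examine whether they impact our proposed primary outcome variables".

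**What is compared by arm.** Under Primary Outcome Variables: "The primary outcome variables will be compared for those in the intervention and those in the comparison arms". The variables then named cover sexual risk behaviour, disclosure, partner testing, alcohol, adherence, STIs, pregnancy and family planning. Violence is not named there, nor in Objectives, Hypotheses or the Data analysis plan.

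**What the package does.** Providers are to "Assess whether patient has disclosed to sex partner(s) and encourage disclosure". Lay counselors offer assisted disclosure to couples. Greater disclosure is one of the behavioural hypotheses.

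**What is measured (Appendix H).**
- J20, for each partner who has been told: "When you told this partner you are HIV-positive did your partner hit, slap, kick, or do anything else to hurt you physically".
- L1: "Have any of your current partners hit, slapped, kicked, or done anything else to hurt you physically". L2 asks the same about anyone else, and L3 asks about forced sex. L1a, L2a and L3a ask whether it happened in the last 6 months.
- H6, on what might follow if others learned the participant's status, has a violent partner as a coded answer.

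**Stated risk.** The section on new or unexpected findings rates the risk to patients as minimal or none. Emergency care adds: "There are no expected harmful consequences as a result of participating in this evaluation".

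**The concern.** The intervention pushes a behaviour, telling a partner, to which violence is a foreseeable reaction. The instrument was written with that in mind: J20 asks about violence at the moment of disclosure, and H6 codes it as a feared result. The analysis then uses violence only to explain the primary outcomes. Whether a mediator affects an outcome is a different question from whether the package changes the mediator, and only the second concerns safety.

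Intended use of study findings says the results will inform scale-up. Under the plan as written, the trial could report more disclosure and more partner testing with no planned estimate of whether violence rose, stayed level or fell. The statement of minimal or no risk would go untested although the data to examine it are collected.

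**Working it through.** **1. Is there any planned arm comparison of violence?** The relevant sections, side by side:

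| Protocol section | Violence mentioned? |
| --- | --- |
| Objectives | No |
| Hypotheses | No |
| Primary Outcome Variables (compared by arm) | No |
| Potential Mediating Variables | Yes; use stated as effect on the primary outcomes |
| Data analysis plan (main model) | No; fixed effects are baseline outcome, country, condition, time and interactions |
| Adverse-event sections | Not named; handled event by event |

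**2. Could adverse-event reporting fill the gap?** Under Roles and responsibilities of project staff, the Site Program Coordinator actively asks about adverse events, but only those associated with the package. The staffing diagram places this coordinator at intervention sites, three per country (its text also carries an unexplained total of six). Project coordinators report unanticipated problems case by case. No summary by arm is described. If enquiry is more active in one arm, counts from this route cannot be compared between arms. The questionnaire is the common source.

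**3. Which items can carry a comparison?**
- J20 is reached only if the participant had sex in the last 3 months (J3) and has told that partner (J18), for at most five partners. Its denominator is people who disclosed, which the intervention is meant to change. It has no time window, and J19 allows the disclosure to have been years ago.
- L1a, L2a and L3a have a 6-month window and do not depend on disclosure. L1 covers current partners only, so a violent partner who has left may appear only under L2.
- L2 and L3 ask about lifetime occurrence and gate L2a and L3a. The Data collection section says some lifetime-occurrence items are not repeated at follow-up, so retention of these items is not assured.

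**4. What precision is available?** The protocol has no figure for violence. Inputs from the sample size section: 9 clinics per arm, 200 enrolled × 0.70 = 140 retained per clinic, ICC .01 or .02, two-sided α = .05. Degrees of freedom are 2(9 − 1) = 16, with t = 2.120.

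Check of the method on the design case (.50 vs .375, ICC .02): the variance inflation is 1 + 139 × .02 = 3.78. SE = √[(.25 + .2344) × 3.78 / 1260] = .0381. Then .125/.0381 − 2.120 = 1.16, which gives power of about 86.8%, consistent with the stated minimum of 80%.

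For violence at a common rate p, SE = √[2p(1 − p)(1 + 139·ICC)/(140 × 9)]. The rates are assumptions.

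| Assumed p | SE, ICC .01 | 95% half-width | SE, ICC .02 | 95% half-width |
| --- | --- | --- | --- | --- |
| 5% | √(.095 × 2.39/1260) = .0134 | 2.8 points | √(.095 × 3.78/1260) = .0169 | 3.6 points |
| 10% | √(.18 × 2.39/1260) = .0185 | 3.9 points | √(.18 × 3.78/1260) = .0232 | 4.9 points |
| 20% | √(.32 × 2.39/1260) = .0246 | 5.2 points | √(.32 × 3.78/1260) = .0310 | 6.6 points |

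Increases detectable with 80% power, using p₁q₁ + p₂q₂ in the variance:

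| Assumed comparison rate | ICC .01 | ICC .02 |
| --- | --- | --- |
| 2% | 5.5% | 6.7% |
| 5% | 9.8% | 11.3% |
| 10% | 16.2% | 18.0% |
| 20% | 27.9% | 30.0% |

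From 5% to 10% the detectable increase is thus about 5 to 8 points.

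**The case against.** The strongest reply is that this is detail for a statistical analysis plan, which was not available for this review. Neither the mediator list nor the outcome list is worded as closed, and a full mediation analysis would normally estimate the effect of arm on each mediator. This stands as a limit on wording: the point is that the protocol states no comparison, not that none could ever be made. It does not remove the point, because the protocol assigns violence a role, and the use stated for that role does not answer the safety question.

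Three stronger readings are tempting but unsupported.
- **That the mediator role would hide harm.** The intention-to-treat model does not condition on violence, so nothing in it masks an effect. The estimate is simply not planned.
- **That harms are picked up only if someone volunteers them.** The Site Program Coordinator must ask. The weakness is the absence of an arm comparison and the apparent placement at intervention sites.
- **That the protocol shows disclosure causes violence.** H6 records participants' fears, and the background section mentions loss of home or livelihood, not violence. The harm is foreseeable, not established.

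The Emergency care statement is also weaker evidence than it looks. It concerns taking part in the evaluation, whereas the package reaches all clinic patients.

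Limited precision is a fair criticism too. At ICC .02 the half-width is about half the assumed 10% rate. That argues for reporting an interval and against reading a null result as safety. It does not argue for leaving the estimate out.

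**Conclusion.** The point holds. As written, the protocol measures violence in both arms, promotes a behaviour that may provoke it, and plans no comparison of it between arms. The finding rests on the text and needs no numerical assumption.

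The precision figures do rest on assumptions: violence rates that the protocol does not give, the protocol's ICCs carried over to a different variable, 140 retained per clinic, and L1a to L3a being asked at follow-up. Under these the comparison is feasible but blunt. It would detect or exclude fairly large increases, not small ones. The change is worth making because it alters what the trial can conclude about the package, using items already in the questionnaire.

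**What to change.** 1. Name physical and sexual violence as a pre-specified safety outcome. It may also stay a mediator.
2. Compare L1a (current partners), L2a (others) and L3a (forced sex) by arm at 6 and 12 months, under intention to treat, with the same clinic-level mixed model. Use all interviewed participants as the denominator, not only those who disclosed. Report differences with 95% intervals and state the limited precision. Read L1a and L2a together, because a former partner may appear only under L2.
3. State that L1 to L3 and their 6-month items are kept in both follow-up questionnaires, notwithstanding the exemption for lifetime-occurrence items.
4. Report J20 descriptively only, restricted through J19 to disclosures made after baseline, with a caution that the intervention affects its denominator.
5. Do the comparison with the final analysis. Intermediate reviews and analyses rules out examining 6- and 12-month data for intervention effects during the project. Any earlier look at violence by arm, for instance by the Steering Committee, would first have to be reconciled with that section.

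**Cost.** Protocol wording, one results table and a check of the follow-up questionnaires. No new items, visits or participants are needed.
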